**Fig. 1 Fig1:**
[figure not shown]
Study flowchart

Randomisation of hospitals, stratified by metropolitan and rural regions, will be undertaken using Microsoft Excel 2010© randomisation generator. Two rural hospitals were combined into one unit for randomisation because they are in the same Local Health District and their aggregated total number of births in 2012 was similar to the total of the other rural hospital in the study. Face-to-face training will be provided, by members of the research team, to the midwives and medical officers at each site to describe the study and the program. The hospitals will develop their own processes to integrate the GHiP referral into the first antenatal appointment for pregnant women. As part of this process, hospitals in both arms will be required to include initial discussion on the importance of healthy gestational weight gain, the setting of a target weight-gain range for the woman’s pregnancy (as per IOM recommendations), screening of the woman for exclusion criteria and recruitment of women following consent.

Health coaches (primarily dieticians and exercise physiologists) delivering GHiP will be provided with a day’s face-to-face training by clinical experts in dietetics and maternity care, in addition to their usual training. A list of online resources to support the pregnant women will also be available to all health coaches. The clinical experts will also be available for further consultation as required.

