### Study setting

The study will be conducted in the antenatal clinics of five NSW hospitals of which three are rural (Orange Base, Lismore Base and Dubbo Base) and two metropolitan (Liverpool and Blacktown). Hospitals were recruited through an expression of interest process addressed to the general manager of each site in the first instance. Agreement was also obtained from the midwifery unit manager and obstetric lead of the maternity unit at each hospital to ensure local support prior to inclusion. All hospitals are public hospitals accounting for approximately 10 % of the total births in NSW and the demographic characteristics of women attending the two metropolitan and the three rural hospitals are similar within their categories. The hospitals offer a variety of antenatal care options for women including hospital-based, shared care with general practitioners or via community based midwifery group practices. All of these care models require women to attend the hospital for an initial antenatal appointment which usually occurs after 12 weeks of gestation.

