### Sample size

A total of 710 women will be recruited; 177 and 532 pregnant women with a pre-pregnancy BMI of 18.5–24.9 kg/m^2^ (healthy range) and ≥25.0 kg/m^2^ (overweight or obese range) respectively. 248 women will be recruited across the three rural hospitals with 462 recruited at metropolitan hospitals. The higher numbers in metropolitan hospitals is to reflect the larger target population in these areas.

The sample size has been calculated using previous reports of weight gain during pregnancy [10, 13, 33] to detect a difference of 3 kgs in gestational weight gain between intervention and control groups at 80 % power. Attrition rates of 60 % in the coaching arm and 30 % in the information only arm are expected. These rates account for the up to 15 % of women, across both arms, who start the study and go on to develop conditions during pregnancy that exclude them from further participation [34] and, allows for the perception of participant burden in the coaching arm. The relatively high attrition rate is conservative compared with other population based programs.

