### Data analysis

#### Primary objectives

All quantitative data analysis will be based on intention to treat principles. Differences between the two study groups in self-reported weight change from pre-pregnancy weight to weight at 36 weeks gestation and 12 months post birth will be tested using the independent samples *t*-test. The proportions of pregnant women who achieve weight gain within the recommended range and those who return to their pre-pregnancy weight 12 months post birth will be analysed using the *X*^2^ test. The adjusted means of the BMI outcomes at 36 weeks gestation and follow up by BMI category will be compared with the pre pregnancy BMI.

Interview data will be analysed using the thematic analysis approach. The transcribed interviews will be coded by the researchers and if there is a disagreement in the classification of interview responses, the researchers will convene as a group to discuss the discrepancies and revise coding categories if needed. Once agreement is reached, themes and sub-themes will be extracted from the data. Data from the interviews will inform the provision of recommendations for program improvement.

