#### Secondary objectives

Predictors of weight gain within the recommended range at 36 weeks of gestation will be analysed using multilevel linear mixed model. Covariance effects of hospital clusters and study arms will be incorporated into the models as random effects. Then the factors that contribute to BMI outcomes at 36 weeks will be determined with demographic variables, socio-economic status, age, pre pregnancy BMI and parity as the fixed effects.

Changes in dietary scores and confidence to change will be analysed using repeated measures analysis of variance, with the type of intervention and data collection point as between and within subject variables respectively.

Participation and retention in the service and preference for time and length of calls will be analysed using descriptive statistics with reference to the qualitative interview data where appropriate. The recommendations for service improvement will be one of the key themes in analysis of the qualitative data. The referral patterns of the hospitals will also be evaluated to assess recruitment rates with reference to the qualitative interviews with the midwives and doctors to identify the potential barriers and solutions to enhance service participation.

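### Hospitals are randomised within metropolitan and rural strata, but the primary tests pool the regions, so unequal rural shares between arms can shift the estimate if region predicts weight gain

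*Protocol article*

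**What the plan says.** **Randomisation.** Protocol article, Study design (text below Fig. 1): "Randomisation of hospitals, stratified by metropolitan and rural regions, will be undertaken using Microsoft Excel 2010". Region is the only factor stated for allocating hospitals; the BMI strata classify women. There are four randomisation units, two per region: the two metropolitan hospitals, one rural hospital and one rural pair. On the pair: "Two rural hospitals were combined into one unit for randomisation because they are in the same Local Health District". The article adds that the pair's combined 2012 births came close to those of the single rural hospital. No such size comparison is given for the two metropolitan hospitals.

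**Comparability.** Study setting: "the demographic characteristics of women attending the two metropolitan and the three rural hospitals are similar within their categories". Nothing is said about similarity between the two categories.

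**Recruitment.** Sample size: "248 women will be recruited across the three rural hospitals with 462 recruited at metropolitan hospitals". No split by arm within region is given. The same section expects attrition of 60% with coaching and 30% with information only. The Discussion says that recruitment may depend on local factors such as leadership and how individual midwives work.

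**Primary analysis.** Data analysis, Primary objectives: change from pre-pregnancy weight to "weight at 36 weeks gestation and 12 months post birth will be tested using the independent samples" t-test. The proportions within the recommended range and back at pre-pregnancy weight go to a chi-squared test. The adjusted BMI means in the same paragraph name no adjusting variable and are compared with pre-pregnancy BMI, not between arms.

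**Secondary model.** Secondary objectives: a mixed model for predictors of weight gain, with hospital and arm as random effects and "demographic variables, socio-economic status, age, pre pregnancy BMI and parity as the fixed effects". Region is not named.

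**The concern.** Stratifying the randomisation sets up a like-for-like comparison: coaching against information within metropolitan hospitals, and the same within rural hospitals. With two units per region and one of each going to each arm, the units balance. The numbers of women they contribute need not. A t-test and a chi-squared test on the pooled women have no place for a stratum. If one arm ends up more rural than the other and rural women gain differently, part of the regional difference is read as an effect of coaching.

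The 36-week and 12-month means and both proportions are exposed. The shift can favour either arm. Recruiting more women in the same proportions would not shrink it. A standard error corrected for clustering would still sit around a shifted estimate.

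**Working it through.** **Inputs from the article.** 248 rural and 462 metropolitan women; 248 + 462 = 710, and the overall rural share is 248/710 = 34.9%. Target difference 3 kg. Attrition 60% and 30%.

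**Assumptions, because the article gives no figure.** One unit per region in each arm; a metropolitan-rural difference in mean gain, d, of 1-2 kg; the coaching share of recruits in each region. The 710 itself cannot be re-derived, since neither SD nor alpha is stated, but this point does not depend on it.

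**Formula.** Let p_C and p_I be the rural shares of the coaching and information arms. With a common coaching effect, each arm's mean is the metropolitan mean plus (rural share × rural-minus-metropolitan difference), plus the effect in the coaching arm. So:

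pooled difference = coaching effect + (p_C − p_I) × (rural mean − metropolitan mean).

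The second term is the shift; sizes are given below without sign.

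**Recruitment scenarios** (coaching share of metropolitan / rural recruits)

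| Split | Coaching: rural / all | Information: rural / all | Gap in rural share | Shift at d = 1 kg | Shift at d = 2 kg |
|---|---|---|---|---|---|
| 50% / 50% | 124 / 355 = 34.9% | 124 / 355 = 34.9% | 0 | 0 | 0 |
| 60% / 60% | 148.8 / 426 = 34.9% | 99.2 / 284 = 34.9% | 0 | 0 | 0 |
| 60% / 50% | 124 / 401.2 = 30.9% | 124 / 308.8 = 40.2% | 9.2 points | 0.09 kg | 0.18 kg |
| 60% / 40% | 99.2 / 376.4 = 26.4% | 148.8 / 333.6 = 44.6% | 18.2 points | 0.18 kg | 0.36 kg |

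The second row shows that an arm-wide difference in recruitment does no harm. What matters is a coaching share that differs between regions. Against 3 kg, the third row is 3-6% and the fourth 6-12%.

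**Attrition alone can do it.** Start from equal recruitment (124 rural and 231 metropolitan per arm). Suppose coaching attrition is 70% rural and 54.6% metropolitan, which is 60% overall. Completers are 124 × 0.30 = 37.2 rural and 231 × 0.454 = 104.9 metropolitan, so the rural share falls to 37.2/142.1 = 26.2%. If attrition in the information arm does not differ by region, that arm stays at 34.9%. The gap is 8.7 points, or 0.09 kg at d = 1 kg and 0.17 kg at d = 2 kg.

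**Effect on the nominal 5% t-test.** Completers are 0.4 × coaching n and 0.7 × information n; SE = SD × √(1/n_C + 1/n_I); rate = P(|Z + shift/SE| > 1.96), with an assumed SD of 5-7 kg and clustering ignored.
- 60% / 50% split: 5.2-5.4% at 1 kg and 5.7-6.5% at 2 kg.
- 60% / 40% split: 5.7-6.4% at 1 kg and 7.9-10.7% at 2 kg.

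These rates are conditional on the imbalance shown.

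**The case against.** The article gives no regional difference in weight gain. Saying that women are alike within each category does not say that the categories differ. If region is not prognostic, nothing happens. The larger scenario also needs recruitment to tilt in opposite directions in the two regions, whereas the rural units were formed to have similar 2012 births, which points towards an even rural split. Both objections stand. They are why the milder range is shown and why the size is stated conditionally.

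Three stronger readings are tempting, and the documents do not support them.
- *The pooled test is biased over the randomisation, independently of any clustering.* Which unit in a region gets coaching is decided at random. If recruitment does not depend on the arm, swapping the allocation reverses the sign. The shift is therefore an imbalance conditional on the allocation. Region is also an attribute of the hospital, so a regional gap is itself between-hospital variation. The shift can exist with a zero ICC within region, but not with a zero ICC overall.
- *Region is absent from every analysis.* In the secondary model, the hospital random effect may absorb part of it, and the open-ended demographic variables could include it. Neither reaches the primary comparison.
- *Error rates well above 10% are to be expected.* A 65% / 35% split with a 2 kg gap would give 12-18%, but nothing in the article makes that combination likely.

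This is also not a detail left to an analysis plan: the article names the two primary tests outright.

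**Conclusion.** The mismatch is real: region is the randomisation stratum for hospitals, and both primary arm comparisons ignore it. Its consequence is conditional. It needs a regional difference in weight gain and a coaching share of recruits or completers that differs between regions. For an assumed 1-2 kg regional difference, the shift runs from about 0.09-0.18 kg (rural even, metropolitan 60/40) to 0.18-0.36 kg (60/40 in opposite directions). That is modest against 3 kg, and it is zero if either condition fails. The change is worth making because it costs almost nothing and restores the comparison that the randomisation set up. It is secondary to the failure of the same tests to allow for clustering with four randomised units.

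**What to change.** **Data analysis, Primary objectives.** For the weight-change means, compare the arms in a model with region as a fixed effect that also handles the hospital clusters. For the proportions, use a region-stratified (Mantel-Haenszel type) estimate, with its uncertainty also allowing for the clusters. Report the metropolitan and rural differences beside the combined estimate.

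State how the regions are weighted. Combining the two differences with fixed weights of 462:248 is not the same as a region fixed effect, which weights by information; the two differ if the coaching effect differs by region.

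**Secondary objectives.** Name region among the fixed effects.

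**Cost.** No new data are needed, because each woman's hospital gives her region. One degree of freedom is lost. At woman level that is trivial. In a cluster-level test on four units it takes 4 − 2 = 2 df down to 4 − 3 = 1, and the two-sided 5% critical t rises from 4.30 to 12.71. There, report the region-stratified point estimate and state the choice of degrees of freedom in advance. Adding region alone leaves the clustering problem untouched, so the two changes should be made together.

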**Methods/Design:**

This study aims to compare the effectiveness of a telephone-based health coaching program versus provision of information only in supporting pregnant women to achieve appropriate gestational weight gain. A pragmatic stratified clustered randomised controlled trial will be conducted with 710 women who present to 5 hospitals for their first antenatal appointment during the recruitment period (6–8 months), have a pre-pregnancy body mass index (BMI) ≥ 18.50 (healthy weight or above), are 18 years and over, singleton gestation, English speaking, have no pre-existing medical conditions that may limit their ability to exercise or require a restricted diet and are 18 weeks or less gestation. Hospitals will be randomised into one of two intervention models: a) information only; or b) information plus 10 telephone-based health coaching sessions with a university qualified coach. Both interventions will set a weight-range target with pregnant women. The women attending antenatal clinics at participating hospitals will be screened at their initial hospital appointment to assess their eligibility. Women recruited to the trial will have a number of measures recorded including anthropometrics (self-reported height and weight) and dietary and physical activity scores during and following pregnancy. These measurements will be collected at baseline (prior to 18 weeks gestation), 36 weeks gestation and 12 months post-birth.

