### Study design

This study employs a pragmatic stratified cluster randomised design [31] with stratification by healthy weight and overweight/obese pre pregnancy BMI.

Pregnant women in the study will be allocated to either the information only or health coaching group based on the hospital where they present for antenatal care (Fig. 1). This design was selected to obtain results that can be generalised with high external validity and utility in the real world setting. In this study, the trial environment and processes will be as close as possible to how the program would be rolled out if effective. A range of hospitals in both metropolitan and rural settings, of different sizes and maternity service delivery levels have been chosen to test the scalability of the intervention across the state.

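### Hospitals are randomised as four units, but the primary tests treat women as independent, so error rates exceed the nominal level unless the within-region ICC is essentially zero

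*Protocol article*

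**What the plan says.** The design is clustered. Study design: "This study employs a pragmatic stratified cluster randomised design". Abstract, Methods/Design: "Hospitals will be randomised into one of two intervention models". Under Study design, each woman is "allocated to either the information only or health coaching group based on the hospital where they present for antenatal care".

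The number of units follows from two statements. Study setting lists "five NSW hospitals of which three are rural", the other two being metropolitan. The randomisation paragraph after Fig. 1 describes "Randomisation of hospitals, stratified by metropolitan and rural regions" and adds: "Two rural hospitals were combined into one unit for randomisation". That leaves two metropolitan and two rural units. Four units are randomised, one of each kind per arm.

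The analysis is at the level of the woman. In Data analysis, Primary objectives, change from pre-pregnancy weight to 36 weeks "gestation and 12 months post birth will be tested using the independent samples" t-test. The proportions within the recommended gain range, and those back at pre-pregnancy weight, get a chi-square test. In Secondary objectives: "Changes in dietary scores and confidence to change will be analysed using repeated measures analysis of variance", with intervention type and time point as the only factors.

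Hospital clusters appear once, as a random effect in the secondary model for predictors of weight gain within range.

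**The concern.** The t-test and chi-square test take the spread between individual women as the only source of chance variation. When hospitals are allocated, differences between hospitals also enter the arm contrast. With two units per arm, these differences average out very little.

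The protocol itself gives reasons to expect them. Sites were chosen to differ in size and service level, each hospital develops its own referral process, and the Discussion concedes that leadership, the individual midwife's approach and the organisation of care may influence recruitment. A hospital whose women gain less weight for such reasons would be counted as evidence for coaching. Because the results are meant to inform rapid roll-out across the state, a significant p-value produced this way would matter.

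The secondary multilevel model does not repair this. It concerns predictors, and it lists study arm among the random effects, so as written it gives no cluster-adjusted estimate of the coaching effect.

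**Working it through.** **1. The plan's own figure.** The sample size of 710 (3 kg, 80% power) cannot be reproduced from the article, which gives no SD, alpha or design effect. Individual-level formulas can reach it. With an assumed SD of 9 kg and two-sided alpha 0.05, n = 2 × (1.96 + 0.84)² × 9² / 3² ≈ 142 per arm, and 142 / 0.4 = 355 per arm gives 710. With the stated 60%/30% losses, 710 instead implies an SD of about 10.2 kg. So 710 neither shows nor excludes an allowance for clustering, and nothing below depends on it.

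**2. Inputs.**
- Sample size section: 462 metropolitan and 248 rural women; attrition 60% (coaching) and 30% (information only).
- Assumed: equal enrolment per unit within region (231 and 124), equal arms (355 each), two-sided alpha 0.05.
- ICC (ρ): not given; range 0.001 to 0.05 assumed.

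**3. Completers.** Coaching: 231 × 0.4 = 92.4 and 124 × 0.4 = 49.6, total 142. Information only: 231 × 0.7 = 161.7 and 124 × 0.7 = 86.8, total 248.5.

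**4. Variance of the difference in pooled arm means** (total variance set to 1).
- Assumed by the t-test: 1/142 + 1/248.5 = 0.01107.
- With a unit effect, each arm contributes ρ × Σw² + (1 − ρ)/n, where w is a unit's share of its arm. In both arms Σw² = (231/355)² + (124/355)² = 0.545.
- True variance = 2 × 0.545ρ + (1 − ρ) × 0.01107. At ρ = 0.01 this is 0.01091 + 0.01096 ≈ 0.0219, so the ratio is 0.0219 / 0.01107 = 1.98.

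**5. Type I error** = 2 × [1 − Φ(1.96 / √ratio)].

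| ICC | Variance ratio | SE too small by factor | Type I error | Simulated (4,000 trials) |
|---|---|---|---|---|
| 0.001 | 1.10 | 1.05 | 6% | 6% |
| 0.005 | 1.49 | 1.22 | 11% | 11% |
| 0.01 | 1.98 | 1.41 | 16% | 16% |
| 0.02 | 2.95 | 1.72 | 25% | 25% |
| 0.05 | 5.88 | 2.42 | 42% | 42% |

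Better follow-up worsens this. With all 355 women per arm analysed, the error is about 7%, 25%, 37% and 55% at ICC 0.001, 0.01, 0.02 and 0.05.

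**6. What four units can support.** A t-test on unit means has 4 − 2 = 2 df (critical value 4.30), or 1 df with region fitted (12.7). With an assumed SD of 6 kg, its 2-df power for 3 kg is about 53%, 45%, 35% and 22% at ICC 0.005, 0.01, 0.02 and 0.05. The test that ignores clustering appears to have more than 99%. Stratified allocation of 2 + 2 units has 2 × 2 = 4 outcomes, so the smallest two-sided randomisation p-value is 2/4 = 0.50.

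**7. Mixed model.** In 1,500 simulated trials per ICC (unit means, known residual variance, no region term), the REML between-unit variance was zero in about 50%, 41%, 30% and 18% of trials at ICC 0.005, 0.01, 0.02 and 0.05. In those trials the fitted model contains no cluster variance.

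**The case against.** Four points can be made for the plan.

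- **The ICC may be small.** Stratification removes the difference between regions, so only the within-region ICC counts, and Study setting describes the women as demographically alike within each hospital category. At ICC 0.001 the error is only about 6%. This stands as a limit on size. A reader might infer that the p-values are certain to be far too optimistic, but without an ICC the documents do not support that. Nor do they show that the ICC is negligible: similar demographics do not mean similar midwifery practice or recruitment.
- **An unseen analysis plan may handle clustering.** This would answer a gap, but the article names the primary tests, and they conflict with its own unit of randomisation.
- **A reader might infer that the sample size ignored clustering.** The article does not show this either way (step 1).
- **The computed figures are for the t-test only.** The chi-square test and ANOVA share the independence assumption, but their error rates were not calculated. The standard-error factors also precede any small-df correction. With the 2-df critical value, the planned intervals are too narrow by about 3.1, 3.8 and 5.3 at ICC 0.01, 0.02 and 0.05 (factor × 4.30/1.96).

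**Conclusion.** The unit of analysis does not match the unit of randomisation in the primary comparison, and this must be corrected. That follows from the text and needs no assumption.

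The size is conditional. It rests on the assumed ICC range, equal enrolment per unit within region and the stated attrition. The inflation is slight at ICC 0.001 and serious from about 0.01 upward. The nominal 5% holds only if the within-region ICC is essentially zero, which the plan neither claims nor supports.

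The stated 80% power for 3 kg is not supported under a cluster-valid analysis. The 53% to 22% range rests in addition on the assumed SD of 6 kg.

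**What to change.** **Primary analysis.** Replace the t-test, the chi-square test and the repeated-measures ANOVA with an analysis of summary means or proportions of the four randomised units, counting the combined rural pair as one unit. Use 2 df, or 1 df if region is fitted, and state the choice in advance.

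**Mixed model.** A model with arm as a fixed effect, a random intercept for randomised unit and small-sample df should be a sensitivity analysis at most, because the between-unit variance is barely estimable from four units.

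**By region.** Report the arm contrast in each region descriptively. With one unit per arm per region, arm and unit are fully confounded, so no confidence interval should be presented there as a test of coaching.

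**Cost.** No new data are needed, but this is more than a change of wording. Intervals become much wider, the power statement in the Sample size section must be restated, and the plan must say that effectiveness conclusions from four units are limited.

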## Methods/Design

### Aims and objectives

This study will compare the effectiveness of a telephone-based health coaching program versus provision of information alone in supporting pregnant women to achieve appropriate gestational weight gain. Pregnant women will be stratified into pre-pregnancy healthy weight and overweight/obese groups. Given the evidence around issues related to excessive weight gain in pregnancy, a pure control group was not included in the study as it was considered inappropriate to not provide information that could be beneficial to maternal and neonatal health.

The hypothesis of the study is that, pregnant women enrolled in the coaching program will be more likely to achieve a healthy gestational weight gain during pregnancy and better maintain their pre-pregnancy weight post pregnancy. Weight-gain that is above the IOM guidelines is considered excessive gestational weight-gain.

The primary objectives of the study are to:i)Compare the differences in gestational weight gain and weight retention at 12 months post birth of participants in the health coaching and information only armsii)Understand the acceptability and experiences of telephone-based coaching amongst pregnant women and antenatal service providers.

As secondary objectives, the study will:iii)Compare changes in diet (fruit, vegetable, fast food and sweetened drink intake)iv)Assess the predictors of service participation and retentionv)Explore service usage patterns such as length of calls and preferred timevi)Assess confidence to changevii)Provide recommendations for program improvement.

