### The interventions

#### Coaching arm

Women in the coaching arm will be enrolled in a full coaching program comprising of up to 10 calls by university qualified coaches (8 during pregnancy and 2 after birth). Health coaches, using behaviour change informed coaching techniques, will in their first call confirm and discuss the woman’s weight range target according to the IOM guidelines, and develop personally relevant lifestyle change goals and actions for participants to achieve their target weight range. In subsequent coaching calls health coaches will ensure that no conditions have presented in the pregnancy that may require medical clearance or adapted advice, revisit goals and revise them accordingly with the participant, help maintain motivation, discuss strategies for overcoming barriers and prevent relapse of healthy behaviours. Health coaches are guided by a range of national and international guidelines for nutrition, exercise and weight-gain targets for pregnancy. The timing of calls is designed to be flexible based on participant preferences and will generally last between 15 and 25 min. A recommended schedule for the pregnancy coaching calls will be used; three in the first 3 weeks, followed by a call every 2–4 weeks until the end of the pregnancy with two calls post birth.

In addition, participants in the health coaching group will be provided with supportive materials including pregnancy specific factsheets on healthy eating, exercise and the benefits of healthy weight-gain during pregnancy and a general information booklet and diary for setting and tracking health goals. Women will receive usual care from their maternity clinicians during the trial with the exception to setting their weight-gain range target and general advice about gestational weight gain at their first antenatal visit with their midwife.

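### Gain to 36 weeks is classed against a range set for the pregnancy, and no test is named for gain above it, so excessive gain is under-counted and a reduction in gain is diluted on the proportion outcome

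*Protocol article*

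**What the plan says.** All references are to the protocol article.

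- **Outcome.** Data analysis, Primary objectives, compares weight change from pre-pregnancy to 36 weeks and to 12 months post birth by t-test. It then tests by chi-square "The proportions of pregnant women who achieve weight gain within the recommended range". Secondary objectives ties the range to the time point: "Predictors of weight gain within the recommended range at 36 weeks of gestation".
- **Range.** Study design requires every hospital to include "the setting of a target weight-gain range for the" woman's pregnancy, following the IOM. No adjustment of that range to 36 weeks is described.
- **Weights available.** Data collection, Quantitative, gives three time points: baseline, 36 weeks and 12 months post-birth. No weight is planned between the last two.
- **Definition.** Aims and objectives hypothesises that coached women will more often achieve a healthy gain. The only category it defines is excess: "Weight-gain that is above the IOM guidelines is considered excessive gestational weight-gain". Primary objectives names no test of that category.
- **Effect size.** Sample size states that the trial is planned "to detect a difference of 3 kgs in gestational weight gain between intervention and control groups at 80 % power".

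**The concern.** There are two separate problems.

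First, a woman weighed at 36 weeks has not finished gaining. If her gain so far is compared with a range meant for the pregnancy, some women who will end above the range are counted as within it, and some who will end within it are counted as below it. The bias has a known direction.

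Second, women outside the range are a mixture of those who gained too little and those who gained too much. An intervention that lowers gain moves some women from above into the range and others from within to below it. The tested proportion records only the net of these two flows. The Background motivates the trial by excessive gain, yet the change in excessive gain has no test of its own.

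At stake is what the trial can conclude on its proportion outcome: the rate of excessive gain it reports, and whether a flat within-range result means that coaching did nothing or that over-gain was exchanged for under-gain.

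**Working it through.** **Inputs from the article.** A 3 kg difference (Sample size). Excessive gain in 38–67 % of women (Background).

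**Inputs assumed, because the article does not give them.** SD σ of gain 5–7 kg. Gain remaining after 36 weeks s = 0.8–2.0 kg (0.2–0.5 kg/week over 4 weeks). Range width w = 4–5 kg, with 6–7 kg as a check. Gain is taken as normal. The planned 710 cannot be used to recover σ: Sample size says only "The sample size has been calculated using previous reports of weight gain during pregnancy", without an SD, alpha or design effect.

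**Step 1: under-count of excessive gain.** Let p be the true share above the upper limit at the end of pregnancy. The limit lies z(1−p) SDs above the mean. At 36 weeks the mean is lower by s, so

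under-count = p − [1 − Φ(z(1−p) + s/σ)].

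- Largest: p = 0.50, s = 2.0, σ = 5. 0.500 − [1 − Φ(0.40)] = 0.500 − 0.345 = 0.155.
- Smallest: p = 0.67, s = 0.8, σ = 7. 0.670 − [1 − Φ(−0.440 + 0.114)] = 0.670 − 0.628 = 0.042.

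Excessive gain is under-counted by about 4 to 15 points.

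**Step 2: over-count of low gain.** The lower limit is the upper limit minus w, so

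over-count = Φ(z(1−p) − w/σ + s/σ) − Φ(z(1−p) − w/σ).

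For p = 0.38, w = 4, σ = 5, s = 2.0: Φ(−0.094) − Φ(−0.494) = 0.462 − 0.310 = 0.152. Over w = 4–5 and σ = 5–7 the result runs from 2.5 to 15.2 points.

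**Step 3: a uniform 3 kg reduction.** Both limits stay fixed and the coaching mean is 3 kg lower. Change in percentage points, coaching minus information only, for σ = 5–6 and w = 4–5:

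| Control share above range | Within range, full-pregnancy gain | Within range, 36-week gain against unscaled range | Above range, full-pregnancy gain |
|---|---|---|---|
| 38 % | −3.4 to −2.0 | −9.1 to −3.9 | −19.7 to −17.0 |
| 50 % | +1.0 to +4.0 | −4.9 to +0.8 | −22.6 to −19.1 |
| 67 % | +5.6 to +10.8 | +2.3 to +8.8 | −23.4 to −19.4 |

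Two cases in full (σ = 5, w = 4.5, full-pregnancy gain):

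- 38 % excess: below 27.6 → 50.2 %, within 34.4 → 31.5 %, above 38.0 → 18.3 %.
- 67 % excess: below 9.0 → 23.0 %, within 24.0 → 33.4 %, above 67.0 → 43.6 %.

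**Step 4: where the net change is zero.** The two within-range shares are equal when the middle of the range lies halfway between the arm means. That gives p = 1 − Φ((w − 3)/(2σ)). For w = 4, σ = 6: 1 − Φ(0.083) = 0.467. For w = 5, σ = 5: 1 − Φ(0.20) = 0.421. So even without the 36-week problem, the change vanishes at a control excess of about 42–47 %, inside the article's own range.

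**Step 5: sensitivity to width.** With w = 6–7 kg, σ = 5–6 and full-pregnancy gain, the within-range change is −0.9 to +2.4 points at 38 % excess and +4.2 to +9.5 points at 50 %. The reversal shrinks or disappears.

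**Step 6: power, ignoring clustering and so optimistic.** Assume 355 women per arm. With the stated attrition, 355 × 0.40 = 142 and 355 × 0.70 = 248.5 are evaluable. For σ = 4–7, w = 4–5 and full-pregnancy gain, power on within range is 0.05–0.14 at 38 % excess (where the difference is negative), 0.04–0.27 at 50 % and 0.17–0.90 at 67 %. On above range it is about 0.87–1.00.

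**The case against.** **Within range is a legitimate outcome.** The article's aim is appropriate gain and its hypothesis is healthy gain. A woman pushed below the range has not achieved that. A reader might infer from Step 3 that the planned test gives the wrong sign for coaching. The article does not support this: if coaching trades over-gain for under-gain, a flat or lower within-range share is a correct answer to the hypothesis. This objection stands, and it is why the outcome should be kept and not replaced.

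**Mean gain is also tested.** The t-test comes first in the analysis section and the sample size rests on it. A 3 kg effect would appear there in full. This stands too. It does not supply an estimate of excessive gain.

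**The negative figures come from less apt inputs.** By plan 532 of 709 women (75 %) are overweight or obese, and the Background reports a higher risk of excess in such women. At 67 % excess every case stays positive. The model also lowers every woman's gain by 3 kg, whereas coaching aims each woman at her own range. This stands as a limit on size: dilution is the general result, and reversal is conditional.

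**Scaling may be in an unseen plan.** The article does not exclude it. But a range set for the pregnancy, applied at 36 weeks with no adjustment mentioned, most naturally reads as unscaled.

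**Timing by arm.** From "The timing of calls is designed to be flexible based on participant preferences" a reader might infer that gestation at the endpoint weight differs between arms. That sentence concerns coaching calls. Data collection sets the endpoint at 36 weeks for both arms, so an arm difference is speculation.

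**Conclusion.** The point holds as a mismatch between range and time of weighing, plus a missing contrast. Followed as written, the plan under-counts excessive gain by about 4 to 15 points and over-counts low gain, assuming 0.8–2.0 kg still to be gained and an SD of 5–7 kg. Separately, pooling under- and over-gain dilutes a uniform 3 kg reduction on the proportion outcome. With a range width of 4–5 kg and an SD of 5–6 kg, pooling alone gives a slightly negative estimate at 38 % excess, no change near 42–47 %, and a positive estimate at 67 %. The unscaled 36-week reading lowers each of these further, but all remain positive at 67 %. The share above the range meanwhile falls by 17 to 23 points.

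These are point estimates under assumed inputs and a uniform shift. They do not show that the trial would find harm, that the planned test is invalid, or that endpoint timing differs by arm.

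**What to change.** 1. Record gestational age at the endpoint weight in both arms.
2. State that gain is classed against the recommended gain scaled to that week, and vary the assumed late weekly rate in a sensitivity analysis.
3. Keep within range as the outcome that matches the hypothesis.
4. Add above range (excessive gain, as already defined in Aims and objectives) as a named, tested contrast.
5. Report below, within and above by arm, so that any fall in over-gain is seen beside any rise in under-gain.

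The cost is one extra data item at the endpoint call, reliance on an assumed late rate of gain, and one additional test whose place among the primary comparisons must be stated. Recruitment and visits do not change.
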